### Exploratory analyses

- Median change from baseline in components of lipid panel at Weeks 48
- Changes in glucose tolerance as measured by the HOMA-IR
- Changes in lipoprotein profile and LDL and HDL particle size and distribution
- Virologic and immunologic response, safety, and tolerability by race/ethnicity, age, gender, and hepatitis C coinfection
- Occurrence of targeted clinical events, including death, AIDS-defining illness, and HIV-1 related events (including the CDC Category B diseases)

#### 2.4.1 Summary of Study Duration

The study will last until fully enrolled (80 patients). The expected duration is about 12 months.

#### 2.4.2 Treatment Plan

Eighty number patients will be randomized 1:1 to one of the two study regimens. The treatment allocations will be unblinded/open-label. The patients will take study medications in the following doses :

**IRB Approved**

**06/24/13**

[figure not shown]

- a. Raltegravir 400 mg twice a day, without regard to food consumption.
- b. Darunavir: 800 mg once daily plus ritonavir 100 mg once daily; administer with food. No recommendation for dosage adjustment in patients with renal or severe hepatic dysfunction.
- c. Tenofovir: 300 mg once daily. No dosage adjustment required for hepatic impairment. Renal impairment:  $Cl_{cr}$  30-49 mL/minute: 300 mg every 48 hours;  $Cl_{cr}$  10-29 mL/minute: 300 mg twice weekly;  $Cl_{cr}$  <10 mL/minute without hemodialysis: No recommendation available; Hemodialysis: 300 mg every 7 days or after a total of 12 hours of dialysis (usually once weekly assuming 3 dialysis sessions lasting about 4 hours each)
- d. Emtricitabine: 200 mg once daily. No adjustment required for hepatic impairment. Renal impairment:  $Cl_{cr}$  30-49 mL/minute: 200 mg every 48 hours;  $Cl_{cr}$  15-29 mL/minute: 200 mg every 72 hours;  $Cl_{cr}$  <15 mL/minute (including hemodialysis patients): 200 mg every 96 hours; administer after dialysis on dialysis days

The investigators will follow the patients according the standard of care. In addition, the patients will be followed according the above flow chart: Study visits will be performed at screening, enrollment (week 0) and weeks 2, 4, 8, 16, 24, 32, 40 and 48.

## 2.5 LIST OF SAFETY MEASUREMENTS

Safety data of serious adverse experiences and drug-related adverse experiences that result in Grade 3 or above laboratory toxicity, lead to treatment interruption, or discontinuation will be collected on case report forms. The laboratory safety assessments should include a chemistry evaluation with serum creatinine, liver function tests, complete blood count and a lipid profile. Additional laboratory assessments would be performed per standard of care at the investigator's discretion. In addition, all patients that experience virological failure or who discontinue from the study early should have the 14-day post-therapy follow-up visit noted on the study flow chart (Section 1.6)

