## 2. CORE PROTOCOL

### 2.1 OBJECTIVES AND HYPOTHESES

#### 2.1.1 Hypotheses

We hypothesize that the virologic efficacy (time to loss of virologic response) at 24 weeks will be at least as high following a regimen of Raltegravir + boosted Darunavir as with a regimen of Tenofovir + Emtricitabine + boosted Darunavir.

We further hypothesize that a regimen of Raltegravir + boosted Darunavir will not result in higher rates of adverse events at 24 weeks than a regimen of Tenofovir + Emtricitabine + boosted Darunavir.

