### Secondary Outcome Measures:

- Percentage of patients with serious adverse experience
- Percentage of patients with drug-related adverse experiences that result in grade 3 or above laboratory toxicity
- Percentage of patients with drug related adverse experiences that lead to treatment interruption
- Time from treatment dispensation to the first development of a Grade 3 or 4 sign, symptom, or laboratory abnormality that is at least one grade higher than at baseline
- Percentage of patients with HIV viral load levels less than 50 copies/ml at 24 and 48 weeks.
- Median CD4 count at 24 and 48 weeks and at virologic failure
- Median change in limb fat by DEXA at week 48
- Percentage of patients with occurrence of fasting hypertriglyceridemia (TG >400) or hypercholesterolemia (TC >240) at week 48
- HIV-1 drug resistance patterns at baseline and at time of virologic failure

For assessment of safety and tolerability, counts and percentages of patients with clinical or laboratory adverse experiences of the following type will be tabulated (1) serious adverse experience, (2) drug-related adverse experiences that result in grade 3 or above laboratory toxicity; (3) drug related adverse experiences that lead to treatment interruption; (4) drug related adverse experiences leading to discontinuation.

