### **3.3 Safety Measurements**

#### **3.3.1 Clinical and Laboratory Measurements for Safety**

Safety data of serious adverse experiences and drug-related adverse experiences that result in Grade 3 or above laboratory toxicity, lead to treatment interruption, or discontinuation will be collected at each visit. It is recommended that the patient be followed for laboratory safety assessment according to the standard of care. Note that laboratory assays are to be evaluated by the investigator's local laboratory. The laboratory safety assessments should include a chemistry evaluation with serum creatinine, liver function tests, and a CBC. Additional laboratory assessments should be performed per standard of care at the investigator's discretion.

In case of grade 3 or 4 laboratory abnormalities, it is recommended to retest within 48 hours for confirmation.

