### 3.3.3 Recording and Reporting of Adverse Experiences

#### 3.3.3.1 All Adverse Events

All adverse events will be documented from the time a signed and dated informed consent form is obtained until completion of the last study-related procedure. Those meeting the definition of serious adverse events must be reported using the Serious Adverse Event Form, including serious adverse events reported to the investigator within 30 days after the subject has completed the last dose of study drug.

All adverse events, regardless of seriousness, severity, or presumed relationship to study therapy, must be documented using medical terminology in the source documents. Whenever possible, diagnoses should be given when signs and symptoms are due to a common etiology (e.g., cough, runny nose, sneezing, sore throat, and head congestion should be reported as "upper respiratory infection"). Investigators must also document their opinion concerning the relationship of the adverse event to study therapy. All measures required for adverse event management must be recorded in the source document.

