**IRB Approved**

**06/24/13**

[figure not shown]

Logistic regression analysis will be used to analyze outcome data to determine the difference between the two regimens. With 40 patients enrolled in each arm, the study has 80% power to rule out a 15% difference in efficacy between the two regimens. This assumes a true response rate of 85% for both treatment groups.

The reasons for failure at week 48 should be the primary reason for the earliest treatment failure. For any visit, subjects who have achieved confirmed virologic success (two consecutive visits with HIV viral load < 50 copies/mL) will be considered successes. All others should be classified into the other appropriate categories listed in Table 2. All events occurring in the window should be considered events for that visit.

All patients who take study medication will be included in the analysis of safety and tolerability. Only those adverse experiences that occur while on study therapy, or within 14 days after discontinuation of study therapy will be included in the analysis.

For assessment of safety and tolerability, counts and percentages of patients with clinical or laboratory adverse experiences of the following type will be tabulated (1) serious adverse experience, (2) drug-related adverse experiences that result in grade 3 or above laboratory toxicity; (3) drug related adverse experiences that lead to treatment interruption; (4) drug related adverse experiences leading to discontinuation.

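### The protocol's CRF safety list and tabulations are narrower than its own any-cause Grade 3/4 outcome and adverse-event hypothesis, so non-serious clinical events would be undercounted

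*Protocol*

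**What the plan says.** Section 2.5 defines what goes on the CRF: "Safety data of serious adverse experiences and drug-related adverse experiences that result in Grade 3 or above laboratory toxicity", together with drug-related events that interrupt or end treatment. Section 3.3.1 repeats the list, with those data to be gathered at every visit ("lead to treatment interruption, or discontinuation will be collected at each visit"). Sections 3.2.3 (reporting to the principal investigator) and 3.2.3.4 (assessments at each visit) use the same list.

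The tabulations in sections 2.4, 2.6 and 3.4 follow it in four categories: serious events, then drug-related events with Grade 3+ laboratory toxicity, with interruption, and with discontinuation.

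Two other statements have no filter on cause:

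- The secondary outcomes in section 2.4 include "Time from treatment dispensation to the first development of a Grade 3 or 4 sign, symptom, or laboratory abnormality", provided it is at least one grade worse than at baseline.
- Section 2.1.1 hypothesises that the raltegravir regimen "will not result in higher rates of adverse events at 24 weeks" than the comparator.

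On masking, section 2.4.2 says: "The treatment allocations will be unblinded/open-label". Section 3.3.3.1 requires every adverse event, of any severity or attribution, to be documented, but in source documents.

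**The concern.** A time-to-first-event outcome is only as complete as the data that feed it. If the CRF omits a class of qualifying events, first events are lost or are dated late, when a later captured event stands in for them. The stated collection rule omits such a class, although the outcome is the protocol's own.

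Two consequences follow. First, undercounting favours a hypothesis that the rate is not higher. If the same share *c* of affected patients is captured in both arms, the observed difference in proportions is *c* times the true one, so it shrinks towards zero. Second, wherever inclusion depends on judged relatedness, *c* may differ between arms, because the person judging knows whether the patient takes the new or the familiar regimen. The direction of that difference cannot be known in advance.

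**Working it through.** The protocol states no figure on this point, so the check sets the rules side by side.

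**Step 1. Which Grade 3/4 events reach the data set?** Every row below counts towards the secondary outcome, provided the event is Grade 3/4 and at least one grade worse than at baseline.

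| Event | On the section 2.5 CRF list? | Other route |
|---|---|---|
| Serious, any cause | Yes | SAE form (3.3.3.1) |
| Laboratory, drug-related | Yes | Scheduled laboratory tests |
| Laboratory, unrelated, non-serious | No | Scheduled laboratory tests (1.6, 3.2.3.4) |
| Clinical, non-serious, related, with interruption or discontinuation | Yes | – |
| Clinical, non-serious, unrelated, patient leaves the study because of it | No | CRF through 3.2.3.5 |
| Clinical, non-serious, unrelated, interruption only | No | Source only; Toxicity Management (3.2.1) asks for a CRF entry only when the interruption is for a drug-related event |
| Clinical, non-serious, unrelated, no consequence | No | Source only |
| Clinical, non-serious, related, none of the listed consequences | No | Source only |

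The last three rows are the gap. All are clinical and non-serious, and one is drug-related, so the gap is not only about attribution.

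**Step 2. Do source documents close the gap?** They preserve the events. But section 3.4.1 gives the CRF the role of collecting uniform data across the two sites, and the protocol describes no route by which events outside the CRF list enter an analysis.

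**Step 3. Does a tabulation match the hypothesis?** Of the four categories, one (serious events) is any-cause and 4 − 1 = 3 are limited to drug-related events. None is an any-cause adverse-event rate, and none is tied to week 24.

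**Step 4. How much rests on attribution?** Section 3.3.2.2 counts an event as drug-associated when it is rated possible, probable or very likely. A rating of doubtful instead of possible therefore moves a non-serious event out of those three categories. Treatment is open-label, so the rating is made with the arm known.

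**Step 5. Safety windows.** Sections 2.6 and 3.4 say that events on therapy or "within 14 days after discontinuation of study therapy will be included in the analysis". Section 3.3.3.1 has serious events reported "within 30 days after the subject has completed the last dose of study drug". The difference is 30 − 14 = 16 days (days 15 to 30).

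**The case against.** The strongest reply is that section 2.5 says what the CRF will hold and never says that it holds nothing else. The flow chart marks adverse events at every visit, section 3.3.3.1 keeps all of them in source, and section 3.4.1 has the principal investigator review them all. Blood count, metabolic profile, liver tests, glucose and lipids are drawn at every scheduled visit with no attribution step. The definition of a serious event in section 3.3.2.2 is broad enough to take in some severe symptoms whatever their cause. Which table answers the hypothesis may also be left to an analysis plan that is not shown.

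Much of this stands, and it rules out several stronger readings:

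- A reader might infer that the CRF excludes every unrelated non-serious event. It does not: section 3.2.3.5 puts study discontinuation for any adverse experience on the CRF.
- A reader might infer that the Grade 3/4 outcome or the hypothesis cannot be answered. The laboratory part can be derived, serious events are captured, and the remaining clinical events can be recovered from source.
- A reader might infer that the 14-day and 30-day windows contradict each other and that late serious events are thrown away. A reporting window and an analysis window serve different purposes, and a shorter analysis window is an ordinary choice. Here it matches the 14-day post-therapy visit in section 2.5. Late serious events are still reported and followed under section 3.3.3.2; they only fall outside the tabulation. A toxicity that causes a patient to stop begins on therapy and so lies inside the window.

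The reply does not remove the gap in Step 1. The same restricted list appears in four sections, and none adds non-serious Grade 3/4 signs and symptoms to the CRF. An analysis plan can add a table, but it cannot tabulate events that were never entered.

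**Conclusion.** The point holds in a limited form. The CRF rule and the safety tabulations are narrower than the any-cause Grade 3/4 outcome and the adverse-event hypothesis. The exposed part is non-serious Grade 3/4 signs and symptoms that are unrelated and do not end study participation, or are related but have none of the listed consequences. For the three drug-related categories, inclusion also depends on open-label attribution.

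This assumes that sites follow section 2.5 as written and enter nothing beyond the list and the study discontinuations of section 3.2.3.5. The size in events or percentage points cannot be derived, because the protocol gives no adverse-event rates and no rate of attribution error. The 16-day difference between windows measures calendar time and not a share of events, so it gives no estimate of lost events. The documents support an undercount of the clinical component. They do not support an unanswerable outcome, discarded serious events or a demonstrated bias between arms.

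**What to change.** In sections 2.5 and 3.3.1, state that all Grade 3 or higher clinical and laboratory events, and all adverse events leading to interruption or discontinuation, are recorded on the CRF regardless of attribution. The entry should carry grade and onset date, since the outcome needs both. Bring the repeated list in sections 3.2.3 and 3.2.3.4 into line.

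In sections 2.6 and 3.4, add an any-cause tabulation by arm, including at week 24, beside the drug-related one.

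Optionally, list separately any serious events and deaths reported on days 15 to 30 after the last dose, leaving the 14-day analysis window as it is.

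The cost is a few more CRF entries. The events are already required in source documents or come from scheduled laboratory tests, and the serious-event reports already exist. No visit or procedure is added.

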## 2.6 DATA ANALYSIS SUMMARY

The primary analysis of efficacy and safety will be based upon the All Patients As Treated (APaT) approach, which includes all patients who received one or more doses of the test drug therapy. All patients who take study medication will be included in the analysis of safety and tolerability. Only those adverse experiences that occur while on study therapy or within 14 days after discontinuation of study therapy will be included in the analysis.

This is an estimation study. The primary endpoint is the comparison of the efficacy of the test regimen (Raltegravir + Darunavir) to Tenofovir + Emtricitabine + Darunavir. The mean effects of the test regimen (Raltegravir + Darunavir) will be compared to comparator regimen.

The analysis will be time to loss of virologic response (TLOVR) [12]. This analysis defines responders as subjects maintaining a minimum of two sequential HIV viral load <50 through the scheduled visits without intervening replicated rebounds or treatment discontinuations.

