## RADAR - Raltegravir And Darunavir Antiretroviral Regimen

- Time from randomization to virologic failure (HIV viral load of 1,000 copies/ml or greater at or after Week 16 and before Week 24, or two consecutive HIV viral load of 50 copies/ml or greater at or after Week 24)

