### **3.2.3.3 Allocation**

Eighty (80) patients meeting the eligibility requirements will be randomized on a 1:1 basis to one of the two treatment groups:

1. Group A: will receive Raltegravir + Ritonavir-boosted Darunavir
2. Group B: will receive Tenofovir + Emtricitabine + Ritonavir-boosted Darunavir

Patients will be provided with medications according to their treatment groups and will be instructed to take them as previously described. The patients will also be instructed on the procedure for reporting of adverse experiences.

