## 3.4 Data Analysis

The primary analysis of efficacy and safety will be based upon the All Patients As Treated (APaT) approach which includes all patients who received one or more doses of the test drug therapy.

The primary endpoint is the comparison of the efficacy of the test regimen (Raltegravir + Darunavir) to Tenofovir + Emtricitabine + Darunavir. The mean effects of the test regimen (Raltegravir + Darunavir) will be compared to comparator regimen.

The analysis will be time to loss of virologic response (TLOVR) [12]. This analysis defines responders as subjects maintaining a minimum of two sequential HIV viral load <50 c/mL through the scheduled visits without intervening replicated rebounds or treatment discontinuations.

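### The primary efficacy set is an as-treated set that requires a dose, in an open-label trial, with no all-randomised analysis and no rule keeping patients in their randomised arm

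*Protocol*

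**What the plan says.** **Analysis set.** Section 3.4 states: "The primary analysis of efficacy and safety will be based upon the All Patients As Treated (APaT) approach". It defines this as an "approach which includes all patients who received one or more doses of the test drug therapy". Section 2.6 gives the same rule, for a set "which includes all patients who received one or more doses of the test drug therapy".

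**Terms.** The next paragraph in both sections ties the word *test* to one arm: "The mean effects of the test regimen (Raltegravir + Darunavir) will be compared to comparator regimen". For safety, section 2.6 uses a broader term: "All patients who take study medication will be included in the analysis of safety and tolerability".

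**Design.** Section 3.2.3.3: "Eighty (80) patients meeting the eligibility requirements will be randomized on a 1:1 basis to one of the two treatment groups". Section 2.4.2: "The treatment allocations will be unblinded/open-label".

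**Outcome.** The primary outcome measure listed in section 2.4 is "Time from randomization to virologic failure", with failure defined by viral-load thresholds. Sections 2.6 and 3.4 describe the analysis as TLOVR, with a responder definition under which stopping treatment is not a response.

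No section names an intention-to-treat or all-randomised efficacy analysis, and none says in which arm an as-treated patient is counted.

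**The concern.** Randomisation makes the two groups comparable at the moment of allocation. A set that also requires a dose selects on something that happens later, and here patient and staff know the allocation when it happens. A patient who is told the arm and does not start disappears from the efficacy denominator instead of counting against the arm. If the two regimens differ in how acceptable they are to patients, this loss can differ between arms.

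The as-treated label adds a second uncertainty. It is often understood to mean grouping by the drug actually received, and the protocol does not rule that out.

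The protocol states this choice in two places, so it is not a detail left open for a statistical analysis plan. A plan that followed the text would inherit it. At stake is the denominator, and possibly the grouping, of the primary comparison in a trial with only 40 patients per arm.

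**Working it through.** **1. Is the set consistent with the rest of the protocol?**

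- *Time origin.* The primary outcome runs from randomisation. A secondary safety outcome in section 2.4 runs from dispensing of treatment, so the protocol distinguishes the two origins. A clock that starts at randomisation fits all randomised patients, not only dosed ones.
- *Outcome categories.* Section 3.4 places every patient without confirmed success in another category of Table 2. Those categories include withdrawn consent, loss to follow-up and nonadherence. A non-starter fits there, but the dosed set removes that patient before Table 2 is filled.
- *Denominator.* The power statement in sections 2.6 and 3.4 assumes 40 enrolled per arm. With 80 patients randomised 1:1, that is the randomised denominator.
- *Discontinuation.* The TLOVR responder definition treats it as non-response. The outcome listed in section 2.4 does not mention it.
- *Terms.* *Test* marks the raltegravir arm, while *study medication* covers both arms. The set is defined with the narrower word.

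**2. How much could it matter?**

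The protocol gives no figure for non-starters, so there is nothing of its own to reproduce. Inputs from the protocol are n = 40 per arm, 85% response in both arms (0.85 × 40 = 34 responders) and a 15-point difference to be ruled out. The number of non-starters, k, is an assumption. Non-starters are taken to be among the 6 non-responders.

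*(a) Non-starters in one arm only.* Dropping k of them changes that arm's rate by 34/(40 − k) − 34/40.

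| k dropped | Rate | Shift in that arm |
|---|---|---|
| 0 | 34/40 = 85.0% | 0 |
| 1 | 34/39 = 87.2% | +2.2 points |
| 2 | 34/38 = 89.5% | +4.5 points |
| 3 | 34/37 = 91.9% | +6.9 points |
| 4 | 34/36 = 94.4% | +9.4 points |

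*(b) Non-starters balanced.* With 2 in each arm, 34/38 − 34/38 = 0, so the between-arm difference does not move. If the arms truly differ, balanced dropping only rescales the difference by 40/(40 − k). For example, 34 against 30 responders gives 4/40 = 10.0 points in all randomised patients and 4/38 = 10.5 points with 2 dropped per arm.

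*(c) Only if patients were regrouped by drug received.* Moving m non-responders from one arm to the other, with 34 responders in each, turns a zero difference into:

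- m = 1: 34/39 − 34/41 = 87.2% − 82.9% = 4.3 points
- m = 2: 34/38 − 34/42 = 89.5% − 81.0% = 8.5 points

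**3. How likely are non-starters?** The flow chart in section 1.6 puts randomisation and first dispensing at the same week 0 visit. Dispensed drug can go untaken, but nothing in the protocol suggests that this would be common.

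**The case against.** **The control arm is not excluded.** A reader might infer from *test drug therapy* that comparator patients fall outside the set. The protocol does not support this. The same sections compare the two regimens and assume 40 patients in each arm, Table 2 has a comparator column, and darunavir is given in both arms. This objection stands: the phrase is a wording defect, not a design error.

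**Regrouping is not stated.** A reader might also take it as settled that patients will be counted by drug taken. The protocol gives only an inclusion rule, no sentence assigns arms by drug received, and the groups are described only as randomised. A plan not shown may settle the matter. This stands too: the fair statement is that the label permits regrouping and nothing excludes it. Calculation (c) is conditional on that.

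**Few exclusions are likely.** Randomisation and dispensing share a visit, and stopping after a first dose still counts as non-response under TLOVR. A dosed set with patients kept in their randomised arms would be a mild departure. This limits the size of the effect but leaves the rule as it is.

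**All-randomised is not always the cautious choice.** This is a pilot estimation study of comparability. Counting never-treated patients as failures in both arms pulls the rates together; with 2 per arm, a difference shrinks by a factor of 38/40. That is a good reason to keep the dosed set as a sensitivity analysis. It does not justify making it the only efficacy analysis.

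**Conclusion.** The point holds in a limited form. Sections 2.6 and 3.4 fix a primary efficacy population that depends on a post-randomisation event, in an open-label trial with an outcome timed from randomisation. They name no all-randomised analysis and do not tie patients to their randomised arm.

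The size of the effect is unknown and may be small. Under the assumption of 34 responders of 40, the first non-starter dropped from one arm adds 2.2 points to that arm's rate, and each further one adds slightly more. With equal response and balanced non-starters the difference does not change.

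A reader might go further and set the 4.5 or 6.9 points for 2 or 3 non-starters against the 15-point difference, concluding that 30% to 46% of it is used up (4.5/15 and 6.9/15). That requires every non-starter to be in the same arm, and the protocol gives no ground for assuming it. Nor does it support saying that the randomised comparison is certain to be materially distorted.

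**What to change.** - **Sections 2.6 and 3.4, efficacy.** Define the primary efficacy set as all randomised patients, analysed in the arm to which they were randomised. State that patients who never start count as non-responders in the TLOVR responder analysis.
- **Section 2.4, primary outcome.** Align the listed outcome with that rule. It is now defined by viral load alone, so it does not say how a patient who never starts, or who stops, is counted.
- **Sections 2.6 and 3.4, as-treated set.** Reword it as patients with at least one dose of any study medication in either arm. Keep it for safety, and report it as a sensitivity analysis for efficacy, as a check on never-treated patients pulling the arms together.

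This costs edits in three sections and no new data, visits or patients. Response rates may come out slightly lower than in the dosed set.
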